### Sample size

2.4

As of the trial planning period in 2025, no randomized controlled trial data are available investigating the effects of robotic-assisted gait training on both gait dynamics and lower-limb muscle function in children with spastic CP classified as GMFCS level IV. Due to the absence of prior randomized controlled trials in children with GMFCS level IV, the effect size for this trial was conservatively estimated based on findings from systematic reviews and meta-analyses in ambulatory children with milder CP (GMFCS I–III). While this introduces some uncertainty, it represents a standard methodological approach in feasibility trials where direct data are unavailable. Reported effect sizes from these studies are consistently large, with Cohen’s d values ranging from 0.8 for gait speed (14) to 1.65 for step length (15) improvements.

Considering the intensive, device-assisted nature of the intervention and the magnitude of improvement observed in related populations, an effect size of Cohen’s d = 1.0 was deemed appropriate for the sample size estimation in this trial. Using G*Power 3.1 software to model a two-tailed independent samples *t*-test with a significance level of 0.05, power of 0.80, and equal group allocation (1:1 ratio), a total of 34 participants (17 per group) were required to detect the hypothesized between-group differences. To accommodate a potential 5% dropout rate, the final recruitment target has been adjusted to 36 participants, ensuring adequate power to detect meaningful effects while accounting for minimal attrition.

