### Data management

2.8

Standardized case report forms will be used to record participant data in both paper and electronic formats. Data will be entered into a secure, password-protected database by trained research assistants and verified by a second reviewer to ensure accuracy. Each participant will be assigned a unique identifier to maintain confidentiality, and only de-identified data will be used for statistical analyses.

All data will be checked for completeness at each assessment point. In the case of missing data, a detailed log will be kept to identify the reasons and patterns of loss. If the amount of missing data exceeds 5%, multiple imputation methods will be applied under the assumption that data are missing at random. Sensitivity analyses will be conducted to assess the robustness of findings across imputed and complete-case datasets.

Descriptive statistics will be calculated for all variables to summarize baseline characteristics and monitor participant flow throughout the trial. Continuous variables will be reported as means ± standard deviations (or medians and interquartile ranges if non-normally distributed), and categorical variables will be presented as frequencies and percentages. Between-group differences at baseline will be tested using independent samples *t*-tests, Mann–Whitney U tests, or chi-square tests, as appropriate.

The primary analysis will follow the intention-to-treat principle, including all randomized participants regardless of adherence or dropout status. A repeated measures ANOVA or linear mixed-effects model will be used to evaluate between-group differences in changes over time for the primary outcomes (GMFM-IS scores and 1-min walk test distance). These models will include group (intervention vs. control), time (baseline, week 12, week 24), and a group-by-time interaction term. Subject-level random effects will account for within-participant correlations.

Exploratory subgroup analyses will be performed to examine the potential moderating effects of age group (6–8 years vs. 9–12 years), sex (male vs. female), and initial GMFM-IS baseline scores. These analyses will use interaction terms in the mixed-effects models to assess whether treatment effects differ across strata. Results will be interpreted with caution due to potential reductions in statistical power and the exploratory nature of these comparisons.

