All statistical analyses will be performed using R, with a two-tailed alpha level of 0.05 considered statistically significant. A detailed statistical analysis plan will be finalized prior to database lock.

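### Age is tested as a moderator in two bands, which discards roughly a quarter of the age information in a 36-child trial; continuous age is a nearly costless replacement

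*Protocol article*

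**What the plan says.** Section 2.8 of the protocol article plans exploratory subgroup analyses by "age group (6–8 years vs. 9–12 years), sex (male vs. female), and initial GMFM-IS baseline scores". On method it says: "These analyses will use interaction terms in the mixed-effects models to assess whether treatment effects differ across strata". The models in question are those for the two primary outcomes, GMFM-IS and 1-minute walk distance: "These models will include group (intervention vs. control), time (baseline, week 12, week 24), and a group-by-time interaction term". Baseline is therefore one of three response visits. Within-child correlation is handled by subject-level random effects, with no statement on whether these are intercepts only. The section does not say whether baseline GMFM-IS enters as a continuous or a grouped variable.

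The same section labels these analyses exploratory and asks for caution because power may be reduced. It leaves a detailed statistical analysis plan to be finalised before database lock. Section 2.3 (Participants) sets the age range at 6 to 12 years, and section 2.4 (Sample size) sets the total at 36 children.

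**The concern.** The age bands are a stated method, not a detail left open. Cutting a known continuous variable into two groups treats a child just under 9 like one aged 6, and a child just over 9 like one aged 12. An interaction test in 36 children has little power to start with, and the section itself gives low power as the reason for caution. Banding adds a loss that could be avoided. What is at stake is the chance of seeing whether benefit changes with age; no primary conclusion depends on it.

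For the GMFM-IS outcome there is a second, smaller awkwardness. Baseline GMFM-IS is a row of the response and also the moderator, so the same number stands on both sides of the model. For the walk test it is only a covariate and the issue does not arise.

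**Working it through.** **The plan's own figure.** Inputs from section 2.4: "an effect size of Cohen’s d = 1.0 was deemed appropriate for the sample size estimation in this trial", two-sided alpha 0.05 and "power of 0.80, and equal group allocation (1:1 ratio". Noncentral t power is 0.781 with 16 per group and 0.807 with 17, so 34 in total is right. Allowing for 5% dropout, 34 / 0.95 = 35.8, which rounds up to 36, as stated. The plan gives no figure for the moderator tests.

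**Information kept by the age bands.** For a linear age-by-treatment interaction, the relative efficiency of the banded test is the squared correlation between the band indicator and age. For uniform age with a share p below the cut, this is [p(1−p)/2]² / [p(1−p)/12] = 3p(1−p).

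| Assumed ages | Calculation | Kept | Lost |
|---|---|---|---|
| Uniform, 6 to under 13, cut at 9 | p = 3/7: 3 × 3/7 × 4/7 = 36/49 | 0.735 | 26.5% |
| Uniform, 6 to 12, cut at 9 | p = 1/2: 3 × 1/4 | 0.750 | 25.0% |
| Whole years 6–12, equal shares | between-band variance 3.5² × 12/49 = 3; total variance 4 | 0.750 | 25.0% |
| Four truncated-normal shapes | numerical | 0.49–0.66 | 34–51% |

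Under the uniform assumption, 36 children inform the age interaction about as well as 36 × 0.735 to 36 × 0.75, or 26 to 27, would with age kept continuous.

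**What this does to power.** Illustration: one change score per child, residual SD 1, 18 per group, uniform ages, linear moderation, two-sided 5% test. With age scaled to a span of 1 (variance 1/12), the standard error of the interaction slope is about √(4 × 12 / 36) = 1.155. A change of 3 SD across the span gives a noncentrality of 3 / 1.155 = 2.60, and banding multiplies this by √0.735 = 0.857, giving 2.23. Simulation adds the chance imbalance of age within groups and, for bands, the age trend left in the residual:

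| Change in effect across the age span | Continuous age | Two bands |
|---|---|---|
| 2 SD | about 36% | about 28% |
| 3 SD | about 67% | about 51% |

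**Baseline GMFM-IS as response and moderator.** Take the three-visit random-intercept model with group × time × baseline and all lower-order terms, and let all visits correlate equally at r. Given baseline, the true variance of the week-24 change is (1−r)(1+r). The model's pooled residual implies (2/3)(1−r)(2+r). The ratio of model to truth is (4+2r)/(3+3r): 1.11 at r = 0.5, 1.04 at r = 0.8 and 1.01 at r = 0.95. It is never below 1, so the standard error is not too small.

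Simulated size of the week-24 interaction test with no true moderation (n = 36, nominal 5%; the correlations and slope variances are assumptions):

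| Data | Baseline GMFM-IS as moderator | Moderator unrelated to outcome |
|---|---|---|
| Equal correlation, 0.5–0.95 | 4.1–5.1% | 5.2–5.5% |
| Serial correlation (AR(1)), 0.5–0.95 | 6.1–10.3% | 8.8–11.1% |
| Varying slopes | 6.3–15.6% | 6.8–15.6% |

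A week-24 ANCOVA with group × baseline stays at 5.1–5.4% throughout. If the time × baseline term is omitted, equal-correlation data give a size of 15% (r = 0.9) to 58% (r = 0.5), because regression to the mean then loads on the treatment interaction.

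**The case against.** The strongest reply is that this is exploratory work, already flagged as low in power in section 2.8 and again in the Discussion, and that prespecified age strata are common and easy to read. The size of the loss also rests on undocumented assumptions. The age distribution is unknown, and if the effect really stepped at age 9, bands would be the better test. The power illustration needs the effect to change by 2 or 3 SD across the age span, which is large beside a planned overall effect of d = 1.0, and the gain is then 8 to 16 percentage points. All of this stands and keeps the priority low. It does not make banding the better default: the caution about power is no reason to give power away, and the strata can still be shown for reading.

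A reader might also infer that using baseline GMFM-IS on both sides of the model inflates the false-positive rate for that moderator. The documents do not support this. With all lower-order terms and equal correlation the test holds its level. Where it does not, the cause is an intercept-only covariance fitted to data with serial correlation or varying slopes, and an unrelated moderator then does about as badly or worse. The protocol does not specify an intercept-only structure, nor does it say that time × baseline will be left out. Such details commonly belong in the analysis plan, which is not shown.

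**Conclusion.** The age point holds. Section 2.8 fixes two bands where a continuous variable is available, at a cost of about 25–27% of the information on a linear age interaction if ages are roughly uniform. The loss was larger, 34–51%, under the truncated-normal age distributions tried, so one quarter is not a general constant. The power figures are illustrations under uniform age and linear moderation.

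The baseline point holds only as a matter of clean specification and only for the GMFM-IS outcome. The double role is real, but no error-rate inflation can be charged to it. Both are low-priority improvements to an exploratory analysis and leave the primary analysis untouched.

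**What to change.** State that age will be tested as a continuous moderator, through group × time × age with all lower-order terms in the mixed model, and that the two age bands will be used for display only.

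For baseline GMFM-IS as a moderator of the GMFM-IS outcome, choose one of two forms: (a) weeks 12 and 24 as the responses, baseline as a continuous covariate, group × baseline as the moderator term and a suitable covariance for the two visits; or (b) the three-visit model with every lower-order term kept, time × baseline included.

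The cost is one or two sentences in the protocol or the analysis plan, with no new data. The one downside is the linearity assumption for age, which can be checked by plotting individual changes against age by group.

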**Methods:**

This two-arm, parallel-group, randomized controlled trial will enroll 36 children aged 6–12 years with GMFCS level IV CP. Participants will be randomized 1:1 to either the intervention group (robotic gait training using the RoboCT Pediatric Lower Limb Rehabilitation Robot) or the control group (usual care as determined by family preference). The intervention group will receive 45-min sessions, three times per week for 24 weeks. Primary outcomes include Gross Motor Function Item Set and walking capacity (1-min walk test). Secondary outcomes include passive ankle joint range of motion, lower-limb muscle morphology via ultrasound, and psychological satisfaction. Linear mixed-effects models will evaluate group-by-time effects under an intention-to-treat framework.

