### Outcomes

2.7

The primary outcome of this study will be gross motor function and walking capacity, assessed at baseline, middle-point, and after the 6-month intervention period. Secondary outcomes will include passive ankle joint range of motion, muscle morphological properties, and psychological satisfaction. All assessments will be conducted by trained evaluators blinded to group allocation.

Gross motor function will be evaluated using the Gross Motor Function Measure–Item Set (GMFM-IS), a validated short-form tool derived from the full GMFM-66, appropriate for assessing changes in children with CP (16). It focuses on key motor tasks across five dimensions: lying and rolling, sitting, crawling and kneeling, standing, and walking, running, and jumping. In this study, trained evaluators will observe children as they perform selected motor tasks from the GMFM-IS. Each task will be scored on a 4-point ordinal scale: 0 = does not initiate; 1 = initiates (<10% of the task); 2 = partially completes (10–99%); 3 = completes the task independently. The assessment will take place in a quiet, controlled environment with standardized instructions and safety precautions. Scores will be entered into the Gross Motor Ability Estimator software to generate interval-level total scores, allowing for sensitive tracking of changes in motor function over time.

To assess functional walking capacity, participants will undergo the 1-min walk test, performed on a marked 20-meter indoor course. Children will be instructed to walk as quickly and safely as possible without running, and the total distance covered in 60 s will be recorded. For participants who require orthoses or walkers, such assistive devices will be permitted during testing, consistent with real-world functionality.

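### Two primary outcomes, a flat two-sided 0.05 and a sample size for one test, with no rule on whether one or both outcomes must be positive

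*Protocol article*

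**What the plan says.** **Number of primary outcomes.** Section 2.8 (Data management) plans group-by-time models "for the primary outcomes (GMFM-IS scores and 1-min walk test distance". The Abstract (Methods) agrees: "Primary outcomes include Gross Motor Function Item Set and walking capacity (1-min walk test". Section 2.7 (Outcomes) names the same two measures in the singular: "The primary outcome of this study will be gross motor function and walking capacity".

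**Significance level.** Section 2.8 closes with one rule: "All statistical analyses will be performed using R, with a two-tailed alpha level of 0.05 considered statistically significant". It gives no split of alpha, no order of testing and no joint-success condition for the two primary outcomes. The next sentence says that a detailed SAP will be finalised before database lock.

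**Sample size.** Section 2.4 uses G*Power "to model a two-tailed independent samples" t-test, "with a significance level of 0.05, power of 0.80, and equal group allocation (1:1 ratio". With one Cohen's d of 1.0, "a total of 34 participants (17 per group) were required to detect the hypothesized between-group differences". Allowing for 5% dropout, the target is 36. The d of 1.0 is chosen against published effects of 0.8 for gait speed and 1.65 for step length in ambulatory children, and it is assigned to neither primary outcome.

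**The concern.** With two primary tests, 0.05 and 80% describe the trial only once it is known what counts as success. If one positive outcome is enough, there are two chances of a false claim, each at the full 0.05. If both are needed, the trial must clear two hurdles, each with about 80% power. The article applies the single-test figures without choosing between these rules.

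The choice could decide the headline result. The Introduction says that independent walking is not the goal for these children, so a gain on GMFM-IS with little change on the walk test is a realistic result. The article does not say whether that would be a positive trial.

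**Working it through.** **Inputs.** From section 2.4: d = 1.0, two-sided alpha 0.05, power 0.80, 17 per arm, 5% dropout. From section 2.8: two primary outcomes and alpha 0.05 for all analyses. Assumed, because the documents do not give them: the correlation between the two outcomes (0 to 0.9 shown) and d = 1.0 on both.

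**Step 1: the plan's own figure.** For a two-sample t-test with n per arm, df = 2n − 2 and the noncentrality is d × √(n/2). At n = 17, df = 32 and the noncentrality is √8.5 = 2.92. Exact noncentral-t power is 0.807. At n = 16 it is 0.781, so 17 per arm is the smallest n that reaches 0.80. Dropout: 34 / 0.95 = 35.8, rounded up to 36. The stated sample size is correct for one test.

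**Step 2: either outcome suffices.** With no true effect on either outcome and independent tests, the chance of at least one significant result is 1 − (1 − 0.05)² = 0.0975. The upper bound at any correlation is 0.05 + 0.05 = 0.10.

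**Step 3: both outcomes required.** With independent outcomes, joint power is 0.807² = 0.651. If all 36 are retained (18 per arm, 0.830 per outcome), it is 0.830² = 0.689.

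**Step 4: correlated outcomes.** Simulation of two t-tests on correlated normal outcomes, 17 per arm, 200,000 replicates per setting:

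| Correlation | At least one false positive (either suffices) | Joint power, d = 1.0 on each (both required) |
|---|---|---|
| 0 | 9.7% | 65% |
| 0.3 | 9.5% | 67% |
| 0.5 | 9.1% | 70% |
| 0.7 | 8.4% | 72% |
| 0.8 | 7.9% | 74% |
| 0.9 | 7.0% | 76% |

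Across this range the first column stays above 5% and the second below 80%.

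**Step 5: what each rule implies.**
- Either suffices, with multiplicity control: at alpha 0.025, power per outcome is 0.712 with 17 per arm (0.741 with 18). Keeping 0.80 per outcome at 0.025 would need 21 per arm, that is 42 evaluable and 42 / 0.95 = 44.2, so 45 recruited.
- Both required: 80% joint power under independence needs √0.80 = 0.894 per outcome, which takes 22 per arm, that is 44 evaluable and 44 / 0.95 = 46.3, so 47 recruited. Positive correlation lowers this.

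**The case against.** The strongest reply is that multiplicity is commonly left to the SAP, that one is promised, and that the article condenses a fuller protocol. That would dispose of a complaint about silence alone. It does not dispose of this one, because the article states the 0.05 rule for all analyses and fixes the recruitment target on a single test. A later SAP can add a rule, but in doing so it changes the stated alpha or the meaning of the stated power.

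Other parts of the reply stand and limit the point:

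- A reader might infer that the false-positive rate is simply 9–10%. That holds only up to a correlation of about 0.5. The GMFM-IS includes a walking dimension, so positive correlation with a walk test is plausible and the rate may be lower, though still above 5%.
- A reader might infer that the trial suffers both harms at once. It does not: requiring both outcomes keeps type I error within 5%, and accepting either involves no joint-power loss.
- The singular wording in section 2.7 might be read as a real contradiction. Section 2.8 plainly lists two primary outcomes. What is missing is the rule joining them.
- A reader might infer that the rule will be chosen after the results are seen. The documents do not show this, since the SAP is due before database lock and its content is unknown.
- The article calls the study an initial step and speaks of preliminary evidence, which might excuse testing each outcome separately at 0.05. But section 2.1 says that the trial is designed to evaluate effectiveness, and the Discussion says that the sample size was calculated to detect clinically meaningful changes.

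**Conclusion.** The point holds. Followed as written, either 0.05 is not the trial's false-positive rate or 80% is not its power, depending on a success rule that the article does not give. If either outcome suffices, the family-wise rate is about 7–10%. If both are required, type I error is controlled and joint power is about 65–76%.

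These figures assume 17 evaluable children per arm, the t-test of section 2.4, correlations from 0 to 0.9 and, for joint power, d = 1.0 on both outcomes. A smaller effect on either would lower joint power further. They are not power figures for the three-time-point model in section 2.8.

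It is tempting to conclude that GMFM-IS should be the sole primary outcome and that the 0.80 figure would then be sound. The documents support neither step. Nothing ranks GMFM-IS above walking, and d = 1.0 rests on gait speed and step length, not on GMFM-IS.

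**What to change.** Before any outcome data are seen, state the success rule in the protocol and carry it into the SAP.

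- **If either outcome suffices:** replace the flat 0.05 for the two primary tests with Holm, and restate power at N = 36 as about 71% per outcome at the 0.025 step (17 per arm, d = 1.0).
- **If both are required:** keep 0.05 for each and restate joint power as about 65–76%, naming the assumed correlation and effect sizes.
- **Acceptable alternative:** a fixed sequence, with the order chosen and justified by the investigators. This controls the family-wise error at 5% but does not by itself validate the 0.80 figure.

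The cost is a wording amendment and a less favourable power statement. No extra patients are needed unless the investigators want to restore 80%, for which the recruited totals in step 5 of the working (45, or up to 47) are the guide. Section 2.2 reports no enrolment at manuscript submission. The current status is not shown, so the amendment should be dated against the first outcome data.

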### Ethics and dissemination

2.9

This study protocol has been reviewed and approved by the Ethics Committee of Hunan Normal University (approval number: 2025–506) and will be conducted in accordance with the ethical principles outlined in the Declaration of Helsinki. The trial protocol was prospectively registered in the ClinicalTrials.gov under registration number NCT07049523, dated July 2, 2025.

The intervention poses minimal risk to participants. The robotic exoskeleton system is clinically approved for pediatric rehabilitation and is equipped with comprehensive safety mechanisms, including load-sensitive shutdowns and postural supports. All sessions will be supervised by trained rehabilitation specialists to ensure safe operation. Participants in the intervention group may experience temporary fatigue or discomfort, but serious adverse effects are not anticipated. The potential benefits include improved gait performance, joint mobility, and psychological well-being in children with GMFCS level IV CP, a group that currently lacks access to high-intensity ambulatory interventions. Participants in the control group will not be restricted from pursuing usual care.

All personal data collected during the study will be handled in strict confidence. Participants will be assigned anonymized identification codes, and any linkage to identifiable information will be securely stored and accessible only to the principal investigators. Paper forms will be stored in locked cabinets, and electronic data will be stored on encrypted, password-protected servers. Data access will be limited to authorized research personnel. Final datasets used for statistical analysis will be fully de-identified.

The results of this trial will be disseminated regardless of the direction or statistical significance of findings. Findings will be submitted for publication in peer-reviewed, open-access journals specializing in pediatric rehabilitation, neurodevelopmental disorders, or assistive technologies. In addition, study results will be presented at national and international conferences in pediatric neurology, rehabilitation medicine, and assistive robotics. A plain-language summary of key findings will be prepared and shared with participating families and local rehabilitation centers. No participant-identifying information will be included in any reports or publications.

